## Abstract

**Background:**

Daoyin therapy (DT), an ancient therapeutic approach with a history spanning thousands of years, has traditionally been employed to address musculoskeletal pain and psychosomatic disorders. However, the application of DT for chronic neck pain (CNP) has received limited attention in the existing literature, and systematic randomized clinical trials (RCTs) in this context remain scarce. This manuscript outlines an RCT protocol designed to investigate whether DT is more effective at alleviating CNP in adult individuals compared to other interventions.

**Methods:**

A 12-week RCT was conducted, with participants undergoing randomization into one of three groups: DT, Meditation + Fitness Exercise (M+FE), or a control group. Participants in the DT and M + FE groups attended their respective training classes three times per week for 12 weeks. Participants in the control group were required to attend health education workshops every 2 weeks. Following the 12-week intervention period, all participants underwent follow-up assessments at the 16th week. Outcome measures encompassed the Simplified Chinese Neck Pain and Disability Scale (SC-NPAD) and Visual Analog Scale (VAS) for pain assessment, Static Neck Posture Assessment (SNPA) to evaluate neck and shoulder posture and function, Short Form-36 (SF-36) to assess quality of life, and blood tests measuring 5-Hydroxytryptamine (5-HT), Norepinephrine/Noradrenaline (NE/NA), γ-aminobutyric acid (GABA), Adreno-Cortico-Tropic-Hormone (ACTH), β-Endorphin (β-EP), and Calcitonin-Gene-Related Peptide (CGRP) levels via high-performance liquid chromatography (HPLC), chemiluminescence immunoassay (CLIA), enzyme-linked immunosorbent assay (ELISA), and radioimmunoassay (RIA). Brain activity changes were monitored through MRI scans. Repeated measures analyses of variance (ANOVAs) will be used to evaluate the outcomes at baseline, at the 12th week, and at the 16th week. Generalized Estimating Equation (GEE) models will be applied to analyze changes in outcomes over time and differences between groups.

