### Dropout criteria

Participants who do not successfully complete the clinical protocol for specific reasons are classified as dropouts. These reasons include voluntary withdrawal by the participant, typically due to perceived treatment inefficacy or the emergence of adverse reactions. Participants are considered dropouts if they are lost to follow-up, rendering them inaccessible for necessary assessments. In some instances, researchers may opt to remove a participant from the study due to issues related to poor compliance with study protocols or in cases of serious adverse events that mandate discontinuation of their participation.

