### Interventions

Participants in the DT and M + FE groups attended their respective training classes three times a week for 12 weeks. Coaches instructed and corrected movements during these sessions, teaching Daoyin, meditation, and fitness exercises. Instructional videos were provided to participants for home practice, and participants could send self-recorded videos to coaches via online communication platforms for feedback. Each DT or M + FE exercise classlasted 40 min continuously, excluding warm-up and relaxation time. Assessments were conducted at baseline, at the conclusion of the 12-week intervention period, and again at the 16-week.

Within each class of the DT group, participants underwent Daoyin exercise tailored for neck pain following a 3-step protocol. This protocol included a 10-min warm-up exercise session involving joint and basic Daoyin exercise to prevent sports injuries. The subsequent 40-min Daoyin exercise session comprised guided single, combination, and full-body movements. Finally, a 10-min relaxation exercise sessionfollowed to soothe and relax the body.

Within each class of the M + FE group, participants received a combination of meditation and fitness exercises designed to address neck pain, following a similar 3-step protocol. The warm-up sessionlasted for 10 min and involved joint exercises and basic limb movements. This was followed by a 40-min session consisting of 20 min of guided meditation activities and 20 min of single, combined, and comprehensive fitness exercises focused on neck pain. Lastly, participants engaged in a 10-min relaxation exercise session.

The control group did not receive any specific intervention but were instructed to continue their daily routines. However, participants in the control group were required to attend health education workshops every 2 weeks as part of their study participation.

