### Statistical analyses

Demographic and baseline information will be compared among the different groups. The Kolmogorov-Smirnov test will be employed to assess the normality of data. For intragroup hypothesis testing, differences across various time points will be evaluated using repeated measures analysis of variance (RM-ANOVA) for normally distributed data, and Friedman’s test will be employed for data not following a normal distribution. In the case of intergroup hypothesis testing, normally distributed data will be analyzed using multivariate analysis of variance (ANOVA), while non-normally distributed data will be analyzed using the Kruskal-Wallis H test. Generalized Estimating Equation (GEE) model will be used to assess how the primary outcome measures, SC-NPAD, change over time across the three intervention groups. Covariates such as demographic factors, and other relevant variables will be included in the model to account for potential confounding effects. The GEE model will also be employed to examine the effects of the intervention on secondary outcome measures, such as SNPA scores for neck and shoulder posture and function, SF-36 scores for quality of life, and levels of neurotransmitters (5-HT, NE/NA, GABA, ACTH, β-EP, and CGRP) obtained from blood tests. Similar to the primary outcome analysis, this analysis will consider the longitudinal nature of the data and adjust for potential confounders. The GEE model will estimate the average change in outcome measures over time within each intervention group and to compare the differences in changes between the intervention groups and the control group. Interaction terms may be included in the model to examine whether the effects of the intervention vary over time or across different groups of participants. Appropriate adjustments for multiple comparisons will be made if necessary. Statistical significance will be taken at 2-sided *P* < 0.05. Statistical analyses will be performed using SAS 9.4 (SAS Institute Inc., Cary, NC).

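### RM-ANOVA for within-arm change over weeks 0, 12 and 16 is conditioned only on normality; a mixed model on all observed visits would avoid its reliance on sphericity and complete cases

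*Protocol article*

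**What the plan says.** The abstract (Methods) announces the test for all outcomes: "Repeated measures analyses of variance (ANOVAs) will be used to evaluate the outcomes at baseline, at the 12th week, and at the 16th week". It then gives the longitudinal comparison to a second method: "Generalized Estimating Equation (GEE) models will be applied to analyze changes in outcomes over time and differences between groups".

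The Statistical analyses section is more specific. A Kolmogorov-Smirnov test decides the route, and then: "For intragroup hypothesis testing, differences across various time points will be evaluated using repeated measures analysis of variance (RM-ANOVA) for normally distributed data". Friedman's test is the alternative for non-normal data. No condition other than normality is attached to RM-ANOVA. For the primary outcome the section says: "Generalized Estimating Equation (GEE) model will be used to assess how the primary outcome measures, SC-NPAD, change over time across the three intervention groups". It also gives GEE the average change within each group and the comparison of change with control. The significance rule is: "Statistical significance will be taken at 2-sided *P* < 0.05".

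Three other places matter:
- **Interventions:** "Assessments were conducted at baseline, at the conclusion of the 12-week intervention period, and again at the 16-week".
- **Sample size:** 10% attrition is allowed for, with 20 participants per group.
- **Dropout criteria:** voluntary withdrawal is described as "typically due to perceived treatment inefficacy or the emergence of adverse reactions". Loss to follow-up, poor compliance and serious adverse events are also listed. No rates or timing are given.

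**The concern.** Normality is only one of the conditions for the RM-ANOVA F test. In its uncorrected univariate form, the differences between each pair of visits must also have equal variance (sphericity). Here the gaps are 12, 16 and 4 weeks, treatment fills the first 12 weeks, and the Follow-up section says nothing further is given in the last 4. Scores at weeks 12 and 16 are therefore likely to correlate more strongly with each other than with baseline. The week 12 to 16 difference would then vary less than the other two, and the uncorrected test would reject too often.

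The second issue is who is analysed. Conventional RM-ANOVA drops anyone missing a visit, so a participant seen at week 12 and lost by week 16 loses the observed week-12 value too. If such losses follow a poor response, as the Dropout criteria make plausible, the remaining sample looks better than the randomised one. GEE keeps the observed visits, so the two analyses could describe different participants.

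At stake are the P values and means for within-arm change, for every outcome tested this way.

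**Working it through.** **Inputs from the article.** Three visits; nominal two-sided level 0.05; 20 per arm with 10% attrition, so 20 × 0.10 = 2 lost and 18 completers.

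**Inputs assumed.** Equal variances at the three visits and correlations a (weeks 0–12), b (weeks 0–16) and c (weeks 12–16). The article gives none of these, so a range is used.

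**Step 1: departure from sphericity.** Take two orthonormal contrasts, week 12 against week 16 and baseline against the mean of the other two. Their variances are u = 1 − c and v = (6 − 4a − 4b + 2c)/6, and their covariance is w = (a − b)/√3. Then

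epsilon = (u + v)² / [2(u² + v² + 2w²)].

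- 0.3/0.3/0.90: u = 0.10, v = 5.4/6 = 0.90, w = 0, so epsilon = 1/[2(0.01 + 0.81)] = 0.61.
- 0.5/0.45/0.80: u = 0.20, v = 3.8/6 = 0.633, w² = 0.0025/3 = 0.00083, so epsilon = 0.694/0.886 = 0.78.
- Equal correlations: u = v and w = 0, so epsilon = 1, whatever the visit spacing.

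**Step 2: type I error with complete data.** Null data were simulated for one arm of 18 and the uncorrected F was referred to F(2, 34). Two values in a cell are runs with different seeds and show the simulation error.

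**Step 3: response-related loss after week 12.** From 20 null participants per arm (100,000 data sets), 2 were removed before week 16. They were chosen either by the worst week-12 score (full selection) or by that score plus noise of equal variance (noisy selection).

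| Correlations a/b/c | Epsilon | Complete data, n = 18 | Noisy selection | Full selection |
|---|---|---|---|---|
| 0.6 throughout | 1.00 | 4.9–5.1% | 5.7% | 6.5% |
| 0.6/0.55/0.75 | 0.90 | 5.4–5.5% | 6.0% | 6.7% |
| 0.5/0.45/0.80 | 0.78 | 6.2% | 7.0% | 7.9% |
| 0.4/0.35/0.85 | 0.68 | 6.7–6.8% | 8.2% | 9.5% |
| 0.3/0.3/0.90 | 0.61 | 7.5–7.6% | 9.1% | 10.9% |

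The first row reproduces the nominal 5% with complete data, which checks the code. The Greenhouse-Geisser-corrected test stays at about 4.6% to 5.2% with complete data under the unequal sets.

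**Step 4: ceiling from sphericity failure alone.** The worst case is epsilon = 0.5. The 5% critical value of F(2, 34) is 3.276, and P(F(1, 17) > 3.276) = 0.088. With complete data the within-arm error therefore cannot exceed about 8.8%.

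**Step 5: shift in the completers' mean.** The two largest of 20 standard normal values have expectations of about 1.87 and 1.41. Removing them moves the mean of the other 18 by (1.87 + 1.41)/18 = 0.18 SD. With noise of equal variance the shift is 0.18/√2 = 0.13 SD. The completers' baseline mean moves the same way by a × 0.18. The apparent change from baseline therefore moves by (1 − a) × 0.18, which is 0.07 SD at a = 0.6 and 0.11 SD at a = 0.4.

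**Step 6: random loss.** Removing 2 of 20 at random gave 4.8% under compound symmetry and 5.9% at 0.5/0.5/0.8 (complete data: 6.1%). It adds no inflation.

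**The case against.** The strongest reply is that the article never says the F test will be uncorrected or that incomplete records will be deleted. A sphericity correction and the handling of missing visits are commonly left to an analysis plan, which is not shown. That stands, and a missing correction alone would not be a finding. What remains is that the article names the method and its one condition, when a better and equally simple method exists.

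A reader might infer that the visit schedule proves sphericity fails. It does not: equal correlations at weeks 0, 12 and 16 are spherical, and no covariances are given.

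A reader might also take 9.5% as the error rate of this trial. That figure needs loss after week 12, selected on a poor week-12 score, at one of the stronger assumed correlation sets. The article gives only an overall 10% attrition and lists several reasons for dropout. Someone who withdraws for inefficacy during treatment has no week-12 value to lose, so the lost-data argument does not reach that person.

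Finally, a reader might infer that the treatment comparison is inflated. The Statistical analyses section limits RM-ANOVA to within-arm testing and gives comparisons of change between groups to GEE, which does not need sphericity and uses incomplete records. A group-by-time RM-ANOVA is not planned there.

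**Conclusion.** The point holds in a limited, conditional form. If the within-arm RM-ANOVA is run uncorrected, its type I error is about 5.5% to 7.6% with 18 completers under the assumed unequal correlations, 5% under compound symmetry, and at most 8.8% from sphericity failure alone. If the planned 10% attrition comes after week 12 and depends on a poor week-12 score, rejection is about 6% to 9.5% for the three sets up to 0.4/0.35/0.85 and somewhat higher at 0.3/0.3/0.90. The completers' week-12 mean then looks 0.13 to 0.18 SD better. These sizes rest on assumed correlations and an assumed dropout mechanism that the article makes plausible but does not state.

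The between-group conclusions from GEE, including those for SC-NPAD, are not shown to be affected. This is a cheap improvement to a supporting analysis, not a flaw in the main comparison.

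**What to change.** In the abstract and in Statistical analyses, replace RM-ANOVA with a linear mixed model for repeated measures on all observed visits: unstructured covariance over the three visits, Kenward-Roger degrees of freedom, and within-arm visit contrasts taken from the model. It does not assume sphericity. It keeps the week-12 value of anyone lost later, and it remains valid when dropout depends on scores already observed, provided the model is right.

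If RM-ANOVA is kept, report the Greenhouse-Geisser-corrected P value and label the result a completers' analysis. State that the correction deals with sphericity only and does not remove dropout selection.

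The cost is a sentence of wording in each place and a few lines of SAS (PROC MIXED), with no new data or participants. The downside is that some within-arm P values become slightly larger.

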**Discussion:**

This trial aims to evaluate the efficacy of DT in comparison to other interventions and explore the neuroendocrine mechanisms underlying its effects in adults with CNP. If the intervention and procedures demonstrate feasibility and acceptability, there are plans to conduct a more extensive controlled trial. This could potentially pave the way for the broader application of DT, not only in the context of CNP but also for other chronic diseases.

**Trial registration:**

This trial has been registered with the Chinese Clinical Trial Registry (Registration ID: [ChiCTR2400079571]).

## Background

Chronic neck pain (CNP) constitutes a significant global public health and socioeconomic concern, impacting a substantial portion of the population across their lifespan [1]. The lifetime prevalence of CNP is estimated to be around 50%, and it imposes significant societal and individual burdens [2]. Recent investigations have demonstrated a wide-ranging overall prevalence of CNP, spanning from 0.4% to 86.8% (with an average of 23.1%). Notably, within populations at high risk for CNP, such as sedentary workers, the one-year CNP incidence ranges from 10.4% to 21.3% [3], surpassing the rates observed among blue-collar workers.

This high prevalence and incidence of CNP has spurred research into the underlying mechanisms and neural correlates of chronic pain. Over the years, in the field of neuroimaging studies, the prevailing focus has leaned towards functional connectivity (FC) trials, predominantly utilizing the insula as a pivotal seed point. These endeavors collectively shed light on the disrupted FC between the insula and the default network in individuals afflicted by chronic pain. This disruption underscores the intricate interplay between pain processing, perceptual recognition, and cognitive and emotion-related brain region engagement, thus serving as a foundational basis for delving into central neural aspects of chronic pain [4, 5]. However, the intricate nexus between distinct chronic pain subtypes and their corresponding brain regions introduces a nuanced complexity. A plethora of studies have revealed abnormal activation patterns across diverse brain regions and disruptions in FC among chronic pain patients [4, 6]. 

In the present landscape, functional magnetic resonance imaging (fMRI) methodologies predominantly illuminate brain gray matter dynamics in conditions such as lower back pain, back pain, tension-type headaches, and fibromuscular pain syndrome. These examinations have unequivocally exposed structural modifications within brain gray matter as an accompaniment to chronic pain. However, pertinent research focusing on chronic skeletal muscle pain has presented a distinctive narrative. In a study encompassing 13 patients, no discernible differences in gray matter distribution within brain regions were observed when contrasted with normal subjects [7]. Nevertheless, an augmentation in gray matter volume surfaced in prefrontal and somatosensory regions subsequent to an 11-week cognitive-behavioral intervention [7]. Consequently, the intricate relationship between neural activity within specific brain regions and gray matter configurations in the context of chronic pain, including CNP, necessitates further elucidation.

Additionally, there is compelling evidence linking the neuroendocrine system with pain perception. The N-methyl-D-aspartic acid receptor (NMDA) in the rostral ventromedial medulla (RVM) plays a key role in pain modulation, with receptor phosphorylation leading to enhanced channel conductance and increased synaptic insertion of NMDA receptors [8, 9]. Studies reveal that serotonin injection or inhibiting the serotonin transporter (SERT) in the RVM offers analgesic effects, and blocking serotonin receptors hinders analgesia from periaqueductal gray (PAG) stimulation, while systemic morphine boosts serotonin levels in the RVM [10, 11]. During physical activity, opioid receptor activation curbs NMDA receptor phosphorylation and lowers serotonin transporter expression, ultimately decreasing pain sensitivity [12]. Regular physical activity, by activating opioid and serotonin pathways, thus acts as a preventive measure against heightened pain sensitivity.

As we explore interventions for CNP, exercise therapy emerges as a promising intervention for alleviating CNP, displaying consistent benefits across various exercise modalities, be it isometric or isotonic neck strengthening or endurance exercises [13]. Conversely, the impact of stretching exercises appears more constrained in its efficacy [14]. Furthermore, complementary approaches from the realm of alternative medicine, encompassing practices such as Yoga and Qigong, have garnered attention for their notable effectiveness in addressing neck pain [15–17]. These alternative exercise modalities furnish patients with viable options that deviate from conventional exercises.

Daoyin therapy (DT), rooted in the principles of Traditional Chinese Medicine (TCM), encompasses dynamic musculoskeletal training, synchronized breathing techniques, and meditative practices. TCM functional exercises like Taijiquan, Baduanjin, and Liuzijue all fall under the purview of DT [18], embodying its core tenets. Recognized for its health-enhancing attributes, DT has garnered mounting empirical [19] support for its potential to ameliorate conditions such as back pain [20], chronic cardiovascular disease, and psychological disorders [21]. Notably, while musculoskeletal disorders, including neck pain, have shown anassociation with DT [22], there exists a dearth of comprehensive investigations into the effects of this therapy on individuals afflicted with CNP. Furthermore, the efficacy of DT remains contentious, predominantly stemming from challenges related to treatment precision, variable methodologies, inadequately sized cohorts [23], suboptimal methodological rigor, and inconclusive dosing protocols in extant trials. Nonetheless, the feasibility of imparting DT, along with conventional neck exercises, to larger group settings merits consideration. Not only do group settings foster social support dynamics [24], but they also offer cost-effective alternatives to individualized treatments [25]. 

In light of the aforementioned challenges and the growing interest in DT’s potential for musculoskeletal disorders, including CNP, our study seeks to address these gaps in knowledge. This randomized controlled study aims to assess the efficacy of a 12-week DT intervention on various outcomes, including pain, physical function, mental well-being, and quality of life, while also exploring potential underlying mechanisms of modulation. Our hypothesis postulates that this particular exercise regimen holds the potential to alleviate neck pain in adult individuals. Furthermore, this investigation seeks to elucidate the mechanistic pathways through which DT may exert its pain-reducing effects.

## Methods

### Study design

This study represents an RCT with three distinct groups: the Daoyin Therapy group (DT intervention), the Meditation + Fitness Exercise group (M + FE intervention), and Control group. The Institutional Review Board approval was obtained from the Shanghai University of Sport (Project Number: 102772023RT016). We originally planned to recruit a total of 60 eligible individuals suffering from CNP who would then be randomly assigned to one of these three study arms, ensuring a balanced distribution among them. Prior to participating in the study, all participantswere required to provide written informed consent. The data collection and analysis for outcomes assessment will be carried out by independent researchers who are blinded to participant allocation. The primary treatment center for this trialis situated at Shanghai University of Sport. A schematic representation of the study design can be found in Fig. 1.

**Fig. 1 Fig1:**
[figure not shown]
Trial flow chart. Diagram illustrating the randomized controlled trial protocol

### Study population

The primary target for recruitment in this trial was individuals who were experiencing CNP persisting for more than three months, with no relief for a consecutive period exceeding two weeks. Interested individuals who expressed a desire to participate in the trial underwent a face-to-face interview, either conducted in a reception room within a community activity center or conducted online, depending on their preference. Individuals meeting the inclusion criteria were eligible to enroll in the trial after providing their informed consent through the signing of a consent form. To reach potential participants, we employed various recruitment strategies, including: (1) Placement of informative posters at affiliated hospitals of Shanghai University of Sport and nearby community centers; (2) Utilization of online platforms and digital channels to disseminate information and attract potential participants; (3) Collaboration with relevant agencies and partners to expand outreach efforts.

